### Multiplicity

The primary and the secondary outcome are tested in that order each at the 5% level of significance. If the first test is not significant at the 5% level the null hypothesis of the secondary outcome is accepted without test.

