### Dropout and non-attendance in psychotherapy

The term ‘dropout’ refers to patients that choose to end treatment prematurely. It is a common phenomenon in psychotherapy. A recent comprehensive meta-analysis, analyzing 669 studies and 83,834 adult patients with a non-psychotic disorder, reported that, on average, 19.7% of patients dropped out of psychotherapy. The dropout proportion for a subsample of patients with eating disorders was even higher at 23.9% [5].

Previous research has indicated that patients who discontinue treatment prematurely exhibit poorer treatment outcomes [5,6]. In group therapy especially, dropout not only affects the patients themselves and their therapists, but can also have an adverse effect on the remaining group members, sometimes resulting in a ‘wave effect’ with dropouts begetting other dropouts [6].

Related to dropout is the phenomenon of irregular attendance to treatment sessions. It has been demonstrated that psychotherapy attendance is associated with the outcome of treatment [7-9] and, accordingly, the development and testing of interventions to increase attendance and prevent dropout from psychotherapy is highly relevant.

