### Statistical plan and data analysis

#### **
*Sample size estimation*
**

We are planning a trial of independent experimental participants and control participants randomized at a 1:1 ratio. Unpublished data (Stolpegaard Psychotherapy Centre, routinely collected data) from 138 patients with eating disorders at Stolpegaard Psychotherapy Centre indicate that the mean number of attended treatment sessions is 13.58 and the SD is 5.82 sessions. We expect to find that the participants in the experimental group attend at least three more sessions than the participants in the control group. Using a SD of six sessions, we need to include 64 participants in each group (total 128) to be able to reject the null hypothesis that number of attended treatment sessions in the experimental and control group is equal with probability (power) 80%. The type I error probability associated with the test of this null hypothesis is 5%. We also estimated the sample size using a power of 90%. This resulted in a total of 170 participants (2 × 85 participants). We therefore plan to recruit a minimum of 128 participants, and in order to reduce the risk of type II error, we will aim to recruit up to 170 participants, if possible in the 14 months recruitment period. Power and sample size calculations have been made using the PS Power and Sample Size Calculations program version 3.0.14 [53,54] (Dupont & Plummer, Nashville, USA).

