### Power calculations

We have conducted power calculations for the majority of the secondary and exploratory outcomes (Table 3). Based on unpublished calculations of 176 to 263 previous patients with eating disorders in routine care at Stolpegaard Psychotherapy Centre, the SDs of their post-treatment responses to SCL-90-R and WHO-5 were used. Since the EDE, ORS and SDS are not previously used at Stolpegaard Psychotherapy Centre, power calculation is based on norms from previous studies [55-57].

**Table 3 T3:** Power calculations

**Outcome**	**Minimal relevant difference (points)**	**SD (points)**	**Risk of type I error**	**Power (N = 128)**	**Power (N = 170)**
Eating Disorder Examination (EDE)	0.5	1.33	5%	55.9%	68.3%
Outcome Rating Scale (ORS)	4.5	9.5	5%	75.8%	86.7%
Symptom Check List (SCL-90-R)	0.3	0.67	5%	71.0%	82.8%
WHO-Five Wellbeing Index (WHO-5)	2.5	5.6	5%	70.8%	82.5%
Sheehan Disability Scale (SDS)	3.5	7.1	5%	79.1%	89.2%

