### Statistical analysis plan

The analyses are intention–to-treat analyses using a two-sided significance test at 5%. All analyses will be conducted blinded with the two intervention groups coded as A and B.

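### A non-significant attendance test leaves the EDE hypothesis untested; the plan wrongly says its null hypothesis is accepted, and Table 3 should be labelled as stand-alone power

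*Protocol article*

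**What the plan says.** The Outcomes section names one primary outcome (rate of attendance) and one secondary outcome (EDE global score at the end of the intervention). The Multiplicity section tests them in that order, each at 5%, and gives the consequence of a failed first step: "If the first test is not significant at the 5% level the null hypothesis of the secondary outcome is accepted without test".

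The Power calculations section introduces its table with "We have conducted power calculations for the majority of the secondary and exploratory outcomes (Table 3". The EDE row reads "0.5 1.33 5% 55.9% 68.3": difference, SD, type I error, then power in per cent for N = 128 and N = 170. Neither section connects that power to the testing order. The Outcomes part of the statistical plan makes the analysis adjusted for stratification variables and, where measured, the baseline value the primary result. Table 2 shows a baseline EDE.

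**The concern.** In a fixed-sequence procedure, failure at the first step stops confirmatory testing. The second null hypothesis is then not rejected because it was not examined. Calling it accepted turns a missing test into a finding.

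The EDE score is the only secondary outcome, and the Discussion describes it as the one outcome that can be blinded. The objective covers harms as well as benefits. Followed literally, the rule would settle the symptom question as a null result whenever attendance misses significance, whichever way the EDE data point.

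A second, smaller matter is how Table 3 is read. Under the gate, a formal EDE claim needs both tests to succeed. The tabulated figure is the power of the EDE test on its own, and the table does not say so.

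**Working it through.** **Inputs from the protocol.** Tests are run "using a two-sided significance test at 5" per cent, on "independent experimental participants and control participants randomized at a 1:1 ratio". For attendance, the experimental group is expected to "attend at least three more sessions than the participants in the control group", with SD 6, 64 per arm for 80% power and 85 per arm for 90%. For EDE: difference 0.5, SD 1.33.

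**Step 1: reproduce the plan's figures.** Two-sample t-test, two-sided 5%, noncentral t with noncentrality δ / (SD × √(2/n)).

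| Test | n per arm | Noncentrality | Power | Stated |
|---|---|---|---|---|
| EDE | 64 | 0.5 / (1.33 × √(2/64)) = 2.13 | 56.0% | 55.9% |
| EDE | 85 | 0.5 / (1.33 × √(2/85)) = 2.45 | 68.3% | 68.3% |
| Attendance | 64 | 3 / (6 × √(2/64)) = 2.83 | 80.1% | 80% |
| Attendance | 85 | 3 / (6 × √(2/85)) = 3.26 | 90.0% | 90% |

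Table 3 is therefore stand-alone power, without baseline adjustment, with every randomised patient contributing an EDE score.

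**Step 2: how often the rule declares the EDE null accepted.** If the assumed attendance effect is real: 100 − 80.1 = 19.9% of trials at N = 128, and 100 − 90.0 = 10.0% at N = 170. If feedback does not change attendance at all, the gate closes in 100 − 5 = 95% of trials, whatever happens to symptoms.

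**Step 3: would a tested, non-significant EDE result support no effect?** A true difference of 0.5 would be missed in 100 − 55.9 = 44.1% of trials at N = 128 and 100 − 68.3 = 31.7% at N = 170. It would not, and an untested hypothesis has still less support.

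**Step 4: chance that both tests are significant.** Bivariate normal probability with the step 1 powers as marginals. The protocol gives no correlation between the two test statistics, so a range of 0 to 0.5 is assumed.

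| N | Correlation 0 | 0.3 | 0.5 | Stand-alone |
|---|---|---|---|---|
| 128 | 0.801 × 0.560 = 44.9% | 48.2% | 50.6% | 56.0% |
| 170 | 0.900 × 0.683 = 61.5% | 63.5% | 65.1% | 68.3% |

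The shortfall from stand-alone power is 5.4 to 11.1 points at N = 128 and 3.2 to 6.8 points at N = 170. It is also the proportion of trials in which the EDE data would have been significant but the rule declares the null accepted.

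**Step 5: the planned baseline adjustment.** Adjustment replaces the SD by SD × √(1 − r²), where r is the correlation between baseline and end-of-treatment EDE. The protocol gives no r. With r = 0.5 as an assumption, the SD is 1.33 × √0.75 = 1.15. Stand-alone power rises to 68.3% (N = 128) and 80.3% (N = 170), and the probability that both tests succeed is 54.8–60.3% and 72.3–75.4% over correlations 0 to 0.5. At N = 128 that range straddles the stated 55.9%; at N = 170 it lies above the stated 68.3%.

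**The case against.** The fixed sequence controls the type I error, and *accepted* may be no more than loose shorthand for *not rejected*. The section does not say that the report will announce an absence of effect, and the Outcomes part of the plan has all outcomes analysed by regression, so an EDE estimate should exist anyway. The first point stands: the order of testing needs no change. The rest does not remove the problem, because the sentence positively prescribes a conclusion about the null hypothesis without a test, and producing an estimate elsewhere does not withdraw it.

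On Table 3 the objection is strong. Its columns are labelled as power at N = 128 and N = 170, the figures reproduce, and stand-alone power for a secondary outcome is common practice. The low EDE power is disclosed.

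A reader might go further and infer that Table 3 overstates power because interviews will be lost at the dropout rates cited in the Background, where "The dropout proportion for a subsample of patients with eating disorders was even higher at 23.9" per cent. The protocol does not support that step:

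- The figure is dropout from therapy in the literature. No expected loss of EDE interviews is stated.
- The Participant withdrawal section lets patients leave the intervention without leaving the assessments, the analysis is by intention to treat, and multiple imputation is planned under stated conditions.
- Marking down the ORS row for missing end-of-treatment data would contradict the definition of that outcome, which takes each patient's last available score.

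**Conclusion.** The Multiplicity sentence is wrong as written and should be changed. It would convert an untested hypothesis into a null conclusion in about 20% (N = 128) or 10% (N = 170) of trials even if attendance improves as assumed, for an outcome with stand-alone power of only 55.9% or 68.3%. These figures rest on the protocol's own effect sizes, SDs and group sizes.

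Table 3 contains no arithmetic error. What it lacks is a label. The 45–51% and 61–65% for passing both tests hold on Table 3's own assumptions plus an assumed correlation of 0 to 0.5 between the test statistics. They do not show that Table 3 overstates power under the planned analysis, because baseline adjustment works in the other direction and its strength is not given.

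**What to change.** In the Multiplicity section, replace the conclusion that follows a non-significant first test with: *the secondary outcome is not tested confirmatorily; the adjusted EDE difference and its 95% CI are reported as exploratory, with no conclusion of no effect.*

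Under Table 3, add a note that the figures are stand-alone, unadjusted power with complete data. Optionally, add the EDE power jointly with the attendance test, stating the assumed correlation between the test statistics and, if baseline adjustment is credited, the assumed baseline correlation.

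Both are wording changes. They need no more patients and leave the testing order and the significance level as they are.

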### Missing values

Missing values of the secondary outcome and/or covariates included in its analysis are imputed using multiple imputation (SPSS), if the percent of missing patients is >5% and *P* of Little’s test is <5%. The result of the analysis of the imputed datasets is then the primary result.

The assumption of multiple imputation is that the data are missing at random, i.e., that for a given quantity with missing values, the distribution of observed values of this quantity conditional on values observed of other quantities is the same as the conditional distribution of the values planned to be observed of the quantity, but missing. If this condition is not fulfilled, the results of the multiple imputation will be biased. To obtain the range of plausible bias that may result if the MAR (missing at random) condition is not fulfilled, we will do the following two analyses using single imputations of the outcome performed as a sensitivity analysis: 1) missing values in group A are imputed by the minimum value observed in the material, while missing values in group B are imputed by the maximum value observed, and the two groups are compared; and 2) vice versa.

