### Outcomes

The primary outcome is the rate of attendance. It is defined as the number of group sessions the patient has attended over the number of planned sessions (20 or 25 sessions). If at group session # n (n <20) the therapist decides that the patient needs not attend further sessions, the number of planned sessions is set equal to n. When a patient discontinues treatment early, the therapists decide whether this is in accordance with the treatment plan (categorized as ‘planned withdrawal’ or ‘unplanned withdrawal’).

In the analysis of the rate data, the model fit of a Poisson model and a negative binomial model both with offset equal to log (number of planned sessions) are compared and the best fitting model is chosen provided it fits the data reasonably well. In the analysis of continuous outcomes the univariate general linear model is used. If the assumptions of a regression are not fulfilled, a non-parametric test is used (Mann-Whitney).

All outcomes are analyzed using regression analyses, including the binary intervention indicator. The primary results are those adjusted by the protocol-specified stratification variables and (where measured) the baseline value as covariates. In an exploratory analysis the analyses will be repeated with the categorical variable ID-group (identity code of the group) as an additional covariate, and it will be tested if the outcome depends on the treatment group. Then it will be tested if ID-group and the intervention indicator interact. If so, subgroup analyses of the various treatment groups will be conducted.

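### Imputation of the EDE is made primary only if Little's test is significant, and a minimum/maximum imputation is presented as the plausible range of bias

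*Protocol article*

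**What the plan says.** The Missing values section of the protocol article covers "Missing values of the secondary outcome and/or covariates included in its analysis". These "are imputed using multiple imputation (SPSS), if the percent of missing patients is >5" per cent and, joined by an 'and', P "of Little’s test is <5" per cent. When both conditions hold, "The result of the analysis of the imputed datasets is then the primary result". No method is named for more than 5% missing with a non-significant test, so an unimputed analysis is implied.

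The covariates come from the Outcomes subsection of the statistical analysis plan: results are "adjusted by the protocol-specified stratification variables and (where measured) the baseline value as covariates".

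The sensitivity analysis has this stated aim: "To obtain the range of plausible bias that may result if the MAR (missing at random) condition is not fulfilled". It consists of two single imputations. In one, "missing values in group A are imputed by the minimum value observed in the material" and those in group B by the observed maximum; in the other the roles are reversed.

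**The concern.** Little's test has 'missing completely at random' as its null hypothesis. Failing to reject that null in 128 to 170 patients is weak evidence for it, yet the rule treats it as enough to set imputation aside. With, say, 25% missing and P = 0.06, the imputed analysis would not be primary.

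The article's own reasoning makes completely random missingness hard to assume. The section on dropout and non-attendance links attendance to treatment outcome. The sample size section expects the feedback arm to attend at least three more sessions, against an SD of six. The EDE is an interview at the end of the intervention. Under Multiplicity it is tested only after attendance is significant, so it is tested when the arms already appear to differ in attendance. If patients who stop early also miss the interview, EDE missingness would relate both to arm and to outcome.

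At stake is the credibility of the one secondary outcome in the testing hierarchy. The planned sensitivity analysis was meant to show how far that result could be wrong, but two extreme imputations say little about realistic departures.

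**Working it through.** **The plan's own figures.** Table 3 gives the EDE a relevant difference of 0.5, an SD of 1.33, and power of 55.9% (N = 128) and 68.3% (N = 170). With 64 per arm, SE = 1.33 × √(2/64) = 0.235; 0.5/0.235 − 1.96 = 0.17, so power is 56.6% by the normal approximation and 56.0% by the t-test. With 85 per arm the results are 68.8% and 68.3%. The stated figures reproduce.

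**Inputs that are assumptions.** The article gives no EDE missingness rate. Its nearest figure is treatment dropout in a cited meta-analysis: "The dropout proportion for a subsample of patients with eating disorders was even higher at 23.9" per cent. That rate is used below as one scenario. The strength of the link between attendance and missingness, and between attendance and EDE, is also assumed.

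**Does the gate open, and what does it cost?** Simulation, 1,500 trials per row, N = 128, 23.9% of EDE missing. Mean attendance is 13.6 v 16.6 sessions (SD 6, limited to 0–20). Missingness is logistic in attendance. EDE falls by the given number of SDs per 6 sessions attended. Bias is in EDE points relative to the full-data estimate; positive means towards no effect.

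| Odds ratio of missing per 6 fewer sessions | EDE slope (SD) | Little's P < 5%: baseline, strata, arm | Same, plus attendance | Complete-case bias | Bias, attendance in imputation |
|---|---|---|---|---|---|
| 1.5 | 0.3 | 5% | 19% | +0.009 | −0.002 |
| 2 | 0.3 | 6% | 53% | +0.017 | −0.001 |
| 3 | 0.3 | 9% | 93% | +0.033 | +0.001 |
| 5 | 0.3 | 13% | 100% | +0.046 | +0.002 |
| 2 | 0.5 | 7% | 53% | +0.025 | −0.001 |
| 3 | 0.5 | 9% | 93% | +0.051 | −0.001 |

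The last column uses regression imputation as a stand-in for the multiple-imputation point estimate. With N = 170 and attendance in the test, rejection is 26%, 68% and 98% at odds ratios 1.5, 2 and 3.

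**Is the gate or the imputation model responsible?** A stronger scenario has N = 128, attendance 0.5 SD higher with feedback, EDE correlated −0.4 with attendance and 0.5 with baseline, and about 36% v 24% missing. The full-data effect is −0.205 SD and complete-case −0.153, a loss of 0.052 SD × 1.33 = 0.07 points. A close variant (about 39% v 27% missing) separates the two causes:

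- complete-case: −0.148
- imputation from baseline and arm only: −0.148
- imputation that also uses attendance: −0.195

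Opening the gate without attendance in the model therefore changes nothing. This is to be expected: when only the outcome is missing, imputing it from the analysis covariates adds no information.

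**Minimum/maximum analysis.** With a proportion p missing in each arm, each run shifts the difference by p × (observed maximum − observed minimum). Assuming an EDE mean of 2 and SD 1.33, simulated null trials give:

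| Missing | Shift each way (points) | Null trials 'significant' |
|---|---|---|
| 5% | 0.25 | 15% |
| 10% | 0.50 | 49% |
| 23.9% | 1.24 | 99.8% |

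A rerun gave shifts of 0.27, 0.53 and 1.26. The 23.9% row implies an observed range of 1.24/0.239 = 5.2 points. The simulations in the first table had a wider range and gave −1.67 to +1.44 at 23.9% missing, which is 3.11 points wide, or 3.11/0.5 = 6.2 times the relevant difference.

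**The case against.** Several stronger readings are tempting, and the documents do not support them.

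A reader might infer that imputation will usually be skipped. The article does not say which variables enter Little's test. Where missingness depends only on attendance and the test sees only baseline, its null hypothesis is true and it rejects at its nominal 5% by construction. With attendance in the test and strong dependence, it rejects in 93 to 100% of trials. Moreover, when such a test does not reject, the average complete-case bias is smaller still: 0.006, 0.011 and 0.014 points at odds ratios 1.5, 2 and 3 (slope 0.3, 23.9% missing, N = 128).

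A reader might infer that the gate causes the bias. It does not; leaving attendance out of the imputation model does. Nor does the article confine imputation to the analysis covariates. It lists the variables whose gaps are filled, not the predictors, and its missing-at-random paragraph conditions on other observed quantities without limit. A list of predictors may well be left to the full analysis plan.

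A reader might take 23.9% as the expected EDE loss. It is treatment dropout, and the section on participant withdrawal separates leaving the intervention from leaving follow-up assessment, so someone who drops out of treatment may still give an EDE.

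Finally, the minimum/maximum runs do bound any bias within the observed score range, so it would be wrong to say that they cannot reveal it. At 5% missing the shift is only about 0.25 points.

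All of this stands. It limits the size of the problem, but it does not rescue a significance test as the switch for the primary analysis, or the description of extreme bounds as plausible.

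**Conclusion.** The concern holds in a limited form. Two stated rules are badly fixed.

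- **The gate.** The primary EDE analysis switches on a test whose non-significance establishes nothing at this sample size, and the method when the gate is closed is unstated. At 23.9% missing and N = 128, the gate stays closed in 87 to 95% of simulated trials if only baseline, strata and arm are tested. If attendance is also tested, this runs from 81% (weak dependence) to none (strong dependence).
- **The bounds.** The label overstates what the minimum/maximum runs show. Nothing planned lies between missing at random and the extreme.

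The likely harm is modest. Complete-case attenuation is about 0.02 to 0.07 EDE points towards no effect when dependence on attendance is moderate to strong, and about 0.01 when it is weak. The upper figure is 0.07/0.5 = 14% of the relevant difference and 0.07/0.235 = 0.3 of the standard error at N = 128. All of this rests on assumed missingness and assumed dependence. The attendance outcome and its test are untouched.

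**What to change.** Before the data are analysed:

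1. Delete the Little's-test condition. Make multiple imputation the primary EDE analysis whenever more than 5% of patients lack the EDE or a covariate, and state the method for 5% or less.
2. Name the imputation model: arm, stratification variables, baseline EDE, sessions attended, type of ending (planned or unplanned) and available ORS scores. Step 1 without attendance in the model would not remove the bias. Imputing within arm would also allow for the ORS being on tablet in one arm and on paper in the other.
3. Report the complete-case analysis as a sensitivity analysis.
4. Keep the minimum/maximum runs if wanted, but label them extreme bounds. Add a graded delta-adjusted imputation, varied by arm, and report the tipping point. The article offers no basis for a delta range, so the sponsor should justify one.

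The cost is revised wording and some extra imputation runs. The variables named are already collected.
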